**Randomization:**

Participants will be randomized in a 1:1 ratio. Randomization will be performed within an electronic database system at the time of enrolment using a random number generator, an approach that has been successfully used in other clinical trials. Neither participant, study team, or treating team will be blinded to the intervention arm.

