## Abstract

**Objectives:**

The aim of the RAAS-COVID-19 randomized control trial is to evaluate whether an upfront strategy of temporary discontinuation of renin angiotensin aldosterone system (RAAS) inhibition versus continuation of RAAS inhibition among patients admitted with established COVID-19 infection has an impact on short term clinical and biomarker outcomes. We hypothesize that continuation of RAAS inhibition will be superior to temporary discontinuation with regards to the primary endpoint of a global rank sum score. The global rank sum score has been successfully used in previous cardiovascular clinical trials.

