**Main outcomes:**

**Primary endpoint:**

In this study the primary end point is a global rank score calculated for all participants, regardless of treatment assignment ( score from 0 to 7). Please refer to table 4 in the full protocol. In the context of the current trial, it is estimated that death is the most meaningful endpoint, and therefore has the highest score ( score of 7). This is followed by admission to ICU, the need for mechanical ventilation etc. The lowest scores ( score of 1) are assigned to biomarker changes (e.g. change in troponin, change in CRP). This strategy has been used successfully in cardiovascular disease trials and therefore is applicable to the current trial.

The primary endpoint for the present trial is assessed from baseline to day 7 (or discharge). Participants are ranked across the clinical and biomarker domains. Lower values indicate better health (or stability). Participants who died during the 7th day of the study will be ranked based on all events occurring before their death and also including the fatal event in the score. Next, participants who did not die but were transferred to ICU for invasive ventilation will be ranked based on all the events occurring before the ICU entry and also including the ICU admission in the score. Those participants who did not die were not transferred to ICU for invasive ventilation, will be ranked based on the subsequent outcomes. The mean rank score will then be compared between groups. In this scheme, a lower mean rank score indicates greater overall stability for participants.

Secondary endpoints :

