The key secondary endpoints are the individual components of the primary components and include the following: death, transfer to ICU primarily for invasive ventilation, transfer to ICU for other indication, non-fatal MACE ( any of following, MI, stroke, acute HF, new onset Afib), length of stay > 4 days, development of acute kidney injury ( > 40% decline in eGFR or doubling of serum creatinine), urgent intravenous treatment for high blood pressure, 30% increase in baseline high sensitivity troponin, 30% increase in baseline BNP, increase in CRP to > 30% in 48 hours and lymphocyte count drop> 30%. We will also look at the World Health Organization (WHO) ordinal scale for clinical improvement (in COVID-19) in our data. In this scale death will be assigned the highest score of 8. Patients with no limitation of activity will be assigned a score of 1 which indicates overall more stability (3).

Additionally, we will evaluate the potential effects of discontinuing RAAS inhibition on alternative schedules (longer/shorter than 7 days, intermittent discontinuation) using a mechanistic mathematical model of COVID-19 immunopathology calibrated to data collected from our patient cohort. In particular, we will assess the impact of alternative schedules on primary and secondary endpoints including increases to baseline CRP and lymphocyte counts.

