**Blinding:**

This is an open label study with no blinding.

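### Open label is extended to outcome classification, so the ICU-transfer reason and MACE in the primary score can be coded with the arm known; the likely effect is modest and cheap to reduce

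*Protocol article*

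**What the plan says.** Under Randomization, the protocol article states that "Neither participant, study team, or treating team will be blinded to the intervention arm". Under Blinding it adds "This is an open label study with no blinding". Neither sentence sets outcome classification apart from treatment.

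Under Main outcomes, "the primary end point is a global rank score calculated for all participants, regardless of treatment assignment ( score from 0 to 7"). Death scores 7 and biomarker changes score 1. Of what lies just below death, the article says "This is followed by admission to ICU, the need for mechanical ventilation etc". The remaining values are deferred to table 4 of the full protocol, which is not shown.

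The components are named later in the same part of the article: "The key secondary endpoints are the individual components of the primary components and include the following: death, transfer to ICU primarily for invasive ventilation". ICU transfer appears there as two entries, "transfer to ICU primarily for invasive ventilation, transfer to ICU for other indication". The list also has "non-fatal MACE ( any of following, MI, stroke, acute HF, new onset Afib"), with separate entries for 30% rises in troponin and in BNP.

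Under Objectives, the direction is stated: "We hypothesize that continuation of RAAS inhibition will be superior to temporary discontinuation".

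**The concern.** Holding or continuing a drug on a ward is hard to conceal. Classifying recorded events afterwards is a separate step that can be masked, and the article gives no reason for leaving it open.

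Two boundaries in the primary score call for judgement. The first is the main reason for an ICU transfer. The ranking description puts patients transferred for invasive ventilation in their own tier directly below death, so the stated reason moves a patient between tiers. The second is whether an episode is called MI or acute heart failure, and so MACE, or is recorded only as a troponin or BNP rise, which earns the lowest score. If people who know the arm and expect continuation to do better draw these lines even slightly differently between arms, the mean rank score shifts without any treatment effect.

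**Working it through.** **Text.** Set side by side, the two blinding statements exclude a masked assessor. The words in the primary endpoint description about scoring everyone whatever their assignment mean that both arms are scored; they do not describe masked scoring. The plan therefore takes a position on this point and does not merely leave it to the full protocol.

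**Inputs from the article.** About 40 patients randomised 1:1, so about 20 per arm; a mean rank score compared between arms; a 0 to 7 scale with death at 7 and biomarker changes at 1. The article gives no alpha, power, effect size or SD, so the figure of 40 cannot be reproduced. It is used here only for the arm size.

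**Check 1, normal approximation.** Assumptions: no true effect, two-sided 5% test, score SD of 1.5 to 3.

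- Shift in one arm's mean when k patients are each coded s points differently: k × s / 20.
- Standard error of the difference: SD × √(2/20).
- Rejection probability: 1 − Φ(1.96 − shift/SE) + Φ(−1.96 − shift/SE).

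Example: k = 2, s = 3, SD = 2. The shift is 6/20 = 0.30, the SE is 2 × 0.316 = 0.632, and the ratio is 0.47. Rejection probability is 7.6%.

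| Patients recoded | Points each | Shift | SD 1.5 | SD 2 | SD 3 |
|---|---|---|---|---|---|
| 1 | 1 | 0.05 | 5.1% | 5.1% | 5.0% |
| 1 | 3 | 0.15 | 6.2% | 5.6% | 5.3% |
| 2 | 3 | 0.30 | 9.7% | 7.6% | 6.2% |
| 3 | 3 | 0.45 | 15.8% | 11.0% | 7.6% |
| 3 | 5 | 0.75 | 35.3% | 22.0% | 12.4% |

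The last row is an extreme. The whole distance from a biomarker change to death is 7 − 1 = 6 points, so three recodes of 5 points each would span nearly the full scale.

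**Check 2, simulation.** 6000 null trials per setting, 20 per arm, rank test, each patient scored by the worst tier. MACE was assumed to be worth 4 points, and the component rates were also assumed. Extra patients were coded as MACE in the hold arm only.

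| Extra MACE codings | Mean shift | Rejection rate |
|---|---|---|
| 0 | 0 | 5.0% |
| 1 (5%) | 0.08 | 5.4% |
| 2 (10%) | 0.15 | 6.6% |
| 3 (15%) | 0.21 | 8.5% |
| 4 (20%) | 0.27 | 10.7% |

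The Monte Carlo standard error near 5% is √(0.05 × 0.95 / 6000) = 0.28 percentage points. The 5.4% lies 0.4/0.28 = 1.4 standard errors from 5.0%, so one recoded patient shows no clear effect. The simulated shift for two patients corresponds to 0.15 × 20 / 2 = 1.5 points each, which is why its rates are lower than the 3-point rows of the first table. The ICU-reason boundary was not simulated.

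**The case against.** The strongest reply is that most of the score leaves little to judge. Death is a fact. Kidney injury, the biomarkers and length of stay have numeric thresholds. Whether a patient was invasively ventilated is observable. Once components are coded, ranking is largely arithmetic. Excluding reduced ejection fraction plausibly limits the number of disputed heart failure episodes. Event definitions may stand in the full protocol, and a stated hypothesis is not evidence of biased coding. All of this is fair, and it confines the point to two components.

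A reader might go further and infer three things that the article does not support:

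- That MACE is a high-score item. Its value is in table 4, which is not shown; a high place is only suggested by list order and by biomarkers scoring lowest.
- That the ranking step itself is open to bias. The room for bias is in coding the components, including the ICU reason that fixes the tier.
- That a positive result could not be told apart from assessor bias. Under the simulation, reaching 10.7% takes four of 20 patients miscoded in one arm and none in the other.

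It is also right that hiding the arm in a later export does nothing if unblinded staff have already entered a label such as MI; a rule applied to that label only repeats their judgement. The remedy therefore has to work from source findings.

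What the reply does not answer is that the article rules out masking altogether, although only treatment needs to be open.

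**Conclusion.** The point stands in limited form. As written, the plan leaves the reason for ICU transfer and the line between MACE and a biomarker rise open to coding with the arm known. The text shows a missing protection; it does not show that bias occurred.

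The effect is modest. In the simulation the false-positive rate stays near 5% for one patient recoded in one arm and is about 6.6% to 10.7% for two to four. The normal approximation gives 6.2% to 9.7% for two patients at 3 points, and more if more patients or larger recodes are assumed. All these figures rest on assumed SDs, component rates, MACE value and scoring rule, since the article gives none of the first three and its ranking text counts earlier events as well as the worst one. They indicate an order of magnitude only. This is a cheap improvement in freedom from bias and not a flaw that invalidates the trial.

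**What to change.** Replace the blanket statement under Blinding, and the matching sentence under Randomization, with open-label treatment and masked outcome classification. Then:

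1. Before any scoring, write rules that derive the ICU reason and MACE from objective source fields already collected, for example whether and when invasive ventilation started and the recorded diagnostic findings, and not from a label entered by unblinded staff.
2. Have existing data staff or the statistician apply the rules to a REDCap export in which the arm, RAAS-inhibitor and substitute-drug fields are hidden.
3. Lock all scores before the arm is merged.

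The cost is an export permission, a short set of rules, a scoring program and one revised sentence. No extra reader is needed if the rules rest on source fields. The article describes the trial as still enrolling, so this can be done without touching care or visits.

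There are two limits to acknowledge. The record may still reveal the arm, so masking is imperfect. And stay beyond 4 days and urgent intravenous blood-pressure treatment are decided by the unblinded treating team; masked classification does not remove bias there, and the report should say so.

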**Blinding:**

This is an open label study with no blinding.

**Numbers to be randomised (sample size):**

The approximate number of participants required for this trial is 40 patients (randomized 1:1 to continuation versus discontinuation of RAAS inhibitors). This number was calculated based on previous rates of outcomes for COVID-19 in the literature (e.g. death, ICU transfer) and statistical power calculations.

**Trial Status:**

Protocol number: MP-37-2021-6641, Version 4: 01-10-2020. Trial start date September 1^st^ 2020 and currently enrolling participants. Estimated end date for recruitment of participants : July 2021. Estimated end date for study completion: September 1^st^ 2021.

**Trial registration:**

Trial registration: ClincalTrials.gov: NCT04508985, date of registration: August 11^th^ , 2020

**Full protocol:**

The full protocol is attached as an additional file, accessible from the Trials website (Additional file 1). In the interest in expediting dissemination of this material, the familiar formatting has been eliminated; this Letter serves as a summary of the key elements of the full protocol.

**Supplementary Information:**

The online version contains supplementary material available at 10.1186/s13063-021-05080-4.

## Data Availability

De-identified participant data is stored on a secure password protected red-cap data base. Access to the data base will be controlled by the principal investigator. Access criteria to the final trial dataset will be provided upon written request to the corresponding author/principal investigator on publication.
